#### Hardiness, the Ability to Stay Healthy Under Stressful Conditions

In the literature, global hardiness scores (measured by the DRS-15 scale) in military populations are around 29 (scores can range from 0 to 45). To the best of our knowledge, there are no studies that have evaluated the effect of a prevention program on this variable. Thus, as this is a dispositional measure, we consider a 5% increase as relevant (for questionnaire details see Multimedia Appendix 2).

### Secondary End Points

The evaluation criteria used to meet the secondary objectives are provided in the following sections.

#### Objective 2.1: Vulnerability

We will assess the following regarding vulnerability:

Innate: based on a study of the polymorphism of genes involved in stress regulation mechanisms (see Multimedia Appendix 3). These analyses will not be used in a diagnosis.Acquired: based on miRNAs that target regulatory phenomena established in earlier work (see Multimedia Appendix 4.General psychological and somatic symptomatology (the PHQ-15, HADS, and PCL-5).

#### Objective 2.2: Change in Resilience

We will assess follow-up of the change in scores on composite end point questionnaires: PANAS, Self-Compassion Scale, and DRS-15 at 6 and 12 months after inclusion.

#### Objective 2.3: Change in Psychobiological Biomarkers of Activation and Deterioration

We will assess the following regarding change in physiobiological biomarkers of activation and deterioration:

Indirect markers of oxidative stress: lipoperoxidation markers thiobarbituric acid reactive substances and 8-iso-prostaglandin F2alpha [45,46].Circulating markers of central nervous system activity: GABA, brain-derived neurotrophic factor, kynurenic acid, and dopamine [47-49].Inflammation: proinflammatory cytokines (including C-reactive protein, TNF-alpha, IL23, and IL12), anti-inflammatories (IL10 and IL6), and chemokines [50,51].Hypothalamic-pituitary-adrenal axis: cortisol (analysis of saliva on waking, getting up, and 30 minutes later), catecholamines, and neuropeptide Y [52].Markers of physiological activation (autonomic nervous system): cardiac variability index (temporal, frequency, and nonlinear analysis of the electrocardiogram signal to measure indices of parasympathetic flexibility), and electrodermal conductance (level of tonic activity, and amplitude of phasic activity to assess activation of the sympathetic system and its persistence) [53,54].Psychological: follow-up of perceived stress (Cohen questionnaire) and psychological symptomatology scores (the PCL-5, the HADS, and the BMS).

#### Objective 2.4: Change in Psychosocial Factors

We will assess the following regarding change in psychosocial factors:

Flexibility of coping strategies, Flex Cop [55].Sense of duty, inner correspondence, and peaceful harmony (ICPH) questionnaire [31].Emotional reactivity (scores on the emotional Stroop task are compared with the classic Stroop task before and after the intervention at 4 and 12 months) [56,57]. The aim of this task is to evaluate the flexibility of sympathetic and parasympathetic systems inherent in the emotional response to trauma. The classical Stroop task (baseline) will be followed by the emotional Stroop task (reactivity). No learning effect has been documented with using this experimental modality.Self and public stigma scores of PTSD in the military.Perceived social support (the multidimensional scale of perceived social support) [33], and institutional support (the Sieblod vertical and horizontal cohesion questionnaire).

#### Objective 2.5: Describe Changes in Adherence to the Intervention

Adherence will be assessed using quantitative criteria at 4, 6, and 12 months (the Treatment Motivation Questionnaire). This analysis will be based on (1) an analysis of the processes put in place to operationalize the intervention; (2) a focus group consisting of 8 participants, and 10 individual interviews carried out at 4 and 12 months after inclusion; and (3) a qualitative analysis of discussions that took place during workshops to anchor the practice held at 6 months and 1 year. The latter will also make it possible to identify both obstacles and drivers of adherence.

#### Objective 2.6: Describe User Satisfaction With the URGOfeel System

We will assess user satisfaction with the URGOfeel (Urgothech) application using visual analog scales, and short questionnaires that measure (1) the user experience and (2) its benefits.

### Ancillary Study

We plan to run a qualitative analysis of the transferability of the intervention. The transferability assessment will be carried out at the very end of the research protocol (1 year after inclusion) and will use the transferability and support to the adaptation of health promotion interventions ASTAIRE tool. The aim is to facilitate the transfer of the intervention to other populations, both military and civilian. The intervention could then be tailored to other populations, based on this evaluation. The ancillary study will focus on qualitative details, notably the conditions, obstacles, and drivers facilitating the transferability of the intervention to other populations or other contexts. The criteria required by ASTAIRE will be supplemented by a qualitative evaluation based on interviews (n=20), and a focus group (n=8) at the end of the intervention. To limit bias, we will ensure that participants in the various segments of this ancillary study (ASTAIRE, focus groups, and interviews) are distinct from one another. A summary of the analysis of these criteria (qualitative, Astaire, and quantitative, in the long term) could be used as a guide for future deployments of the intervention.

### Statistical Methods

Continuous variables will be presented as mean and SD, if the distribution is normal (the Shapiro-Wilk test will be used, if necessary). In case of a nonnormal distribution, data will be presented as median, quartiles, and extreme values. Scale variables will be treated as ordinal data and analyzed as above. Depending on the analysis, data may be classed as categorical variables. Categorical variables will be expressed as absolute values and percentages. To control for attrition, calculations will assume 20% of data are missing.

The primary analysis will examine the effectiveness of the prevention program. This will be evaluated by comparing the percentage of responses between intervention and nonintervention groups, using a *χ*^2^ test. Secondary analyses will examine the abovementioned markers. Values for the intervention and the nonintervention group will be compared using a repeated measures ANOVA if the conditions for applying an ANOVA are met. Vulnerability will be initially identified using a cluster analysis of the measured biological variables (a *k*-means or Gaussian model mixture, depending on the distribution). The analysis will seek to identify the most biologically at-risk cluster (vulnerable compared with nonvulnerable). The effect of the intervention as a function of vulnerability status will be evaluated using repeated measures ANOVA, by comparing vulnerable and nonvulnerable groups. Psychosocial variables will be compared between intervention and nonintervention groups using repeated measures ANOVA, if the conditions for its application are met. A regression analysis will aim to test the mediating role of psychosocial determinants in the improvement of the composite score.

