### Objectives of the Research

The main objective is to determine the effectiveness of a biopsychosocial program targeting the resilience (developing stable resources to adapt to occupational demands, in order to cope with TEs) of military personnel in the context of PTSD prevention.

The secondary objective is to better understand interindividual variability regarding the program’s impact. We will study levels of vulnerability at inclusion and their impact on the program’s effectiveness. We will also track postprogram changes in resilience (at 6 and 12 months). In addition, we will evaluate (1) the impact of the program on activation and psychobiological deterioration biomarkers and (2) the psychosocial determinants at 4 months (the end of the program) and 12 months (to evaluate persistence). In addition, we will measure adherence to the intervention at group and individual levels, through an evaluation at the end of the program. Finally, we will examine user satisfaction with the URGOfeel sensor and its application during workshops.

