### Sample Size

The number of participants to be included is not based on an a priori calculation. This is due to the absence of data in the literature regarding the effectiveness of a primary prevention program in the military context, measured using a composite criterion that encompasses affect, self-compassion, and hardiness. In order to determine the sample size needed to observe a significant between-group difference, we used the following parameters: a 2-tailed statistical test; a 55% response rate in the intervention group; a 30% response rate in the nonintervention group (significance *P*=.50; power =0.80). If we take into account potential dropouts (estimated at 20%), each group should consist of 58 individuals, making a total of 116 participants.

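### Repeated measures ANOVA for the secondary outcomes uses only soldiers with every visit, although 20% missing data are expected; a mixed model with visit-specific contrasts fits the objectives better

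*Protocol article*

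**What the plan says.** The Statistical Methods section of the protocol article names repeated measures ANOVA three times:

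- Secondary markers: group values "will be compared using a repeated measures ANOVA if the conditions for applying an ANOVA are met".
- Vulnerability: "The effect of the intervention as a function of vulnerability status will be evaluated using repeated measures ANOVA, by comparing vulnerable and nonvulnerable groups".
- Psychosocial factors: "Psychosocial variables will be compared between intervention and nonintervention groups using repeated measures ANOVA, if the conditions for its application are met".

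No other method is named for these between-group comparisons. The article does not say whether the group effect or the group-by-time effect is the test of interest.

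On missing data, Statistical Methods states: "To control for attrition, calculations will assume 20% of data are missing". Sample Size states: "If we take into account potential dropouts (estimated at 20%), each group should consist of 58 individuals, making a total of 116 participants".

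The objectives are tied to visits. Objectives of the Research asks for the effect on biomarkers and on "the psychosocial determinants at 4 months (the end of the program) and 12 months (to evaluate persistence"). Objective 2.2 follows "PANAS, Self-Compassion Scale, and DRS-15 at 6 and 12 months after inclusion".

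According to Table 1 and the section on the +12-month visit, questionnaires are completed at inclusion and three follow-ups (4, 6 and 12 months). Blood, saliva and emotional reactivity are measured at inclusion and two follow-ups (4 and 12 months).

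**The concern.** Classical repeated measures ANOVA needs a complete row for each soldier. One missed session removes that soldier's attended sessions as well. The article's Discussion itself warns that operational constraints may override the ideal conduct of the study, so scattered missed visits are plausible.

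Two things are at stake. The first is precision, because data already collected go unused. The second is validity: a complete-case analysis can be biased when missingness depends on earlier observed values, whereas a likelihood-based model using those values remains valid under that condition.

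A separate issue is fit to the objectives. The overall tests do not say at which visit the groups differ, and the objectives ask about particular visits.

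**Working it through.** **Inputs.** From the article: 58 per arm and 116 in total; 20% dropout or missing data; three follow-ups for questionnaires and two for biological and autonomic measures. Assumed, because the article does not give them: the missed-visit rate m per follow-up, independence of misses, a complete inclusion visit, and a within-soldier correlation of 0.5 to 0.7.

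**The plan's own figure.** The article gives no sample size or power for the secondary outcomes. Its 58 per arm belongs to the primary endpoint. For 55% against 30%, two-sided 5% and 80% power, the pooled formula gives 61 per arm before dropout and 61/0.8 = 76.25, so 77, after it. Hence 58 including dropout does not reproduce on that basis. That is a separate matter, and here 58 is taken simply as the number enrolled.

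**Step 1: soldiers kept.** Share with complete rows = (1 − m)^k over k follow-ups.

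| m | k = 3 | lost | of 116 | k = 2 | lost | of 116 |
|---|---|---|---|---|---|---|
| 5% | 0.857 | 14% | 99 | 0.9025 | 10% | 105 |
| 8% | 0.779 | 22% | 90 | 0.846 | 15% | 98 |
| 10% | 0.729 | 27% | 85 | 0.810 | 19% | 94 |
| 20% | 0.512 | 49% | 59 | 0.640 | 36% | 74 |

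**Step 2: attended visits thrown away.** Complete soldiers supply (1 − m)^k / (1 − m) = (1 − m)^(k−1) of all attended follow-up visits. At m = 10% this is 0.81 for k = 3 and 0.90 for k = 2. So 19% of attended follow-up visits are discarded for questionnaires and 10% for biological measures.

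**Step 3: precision for change from inclusion to 12 months.** Detectable difference at two-sided 5% and 80% power = 2.80 × √(2(1 − ρ)) × √(2/n) SD. The comparison is between complete rows and all soldiers with both inclusion and 12-month values. A mixed model uses at least the latter.

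- Questionnaires, ρ = 0.6, m = 10%: n = 58 × 0.729 = 42.3 gives 0.545 SD; n = 58 × 0.9 = 52.2 gives 0.49 SD.
- Questionnaires, ρ = 0.6, m = 20%: n = 58 × 0.512 = 29.7 gives 0.65 SD; n = 58 × 0.8 = 46.4 gives 0.52 SD. At ρ = 0.5 the pair is 0.73 and 0.58; at ρ = 0.7 it is 0.56 and 0.45.
- Biological measures, ρ = 0.6, m = 20%: n = 58 × 0.64 = 37.1 gives 0.58 SD against 0.52 SD.

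If the 20% is pure dropout with no scattered misses, complete rows and 12-month pairs are the same 46.4 per arm, and this count shows no gain at 12 months. The gain is then at earlier visits. With dropout spread evenly, 58 × 0.8^(1/3) = 53.8 per arm have 4-month values, against 46.4 complete rows.

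A simulation (58 per arm, ρ = 0.6, constant effect 0.5 SD, 20% of each follow-up missing completely at random) gave 55% and 56% power for complete-case change contrasts at 4 and 12 months, and 86% and 88% for a mixed model. That mixed model assumed a common mean at inclusion and a known covariance. The model proposed below estimates separate inclusion means, so its gain would be smaller. The conclusion does not rest on these figures.

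**Step 4: what the overall tests answer.** With two groups, the group-by-time test has (2 − 1)(4 − 1) = 3 df for questionnaires and (2 − 1)(3 − 1) = 2 df for biological measures. It does not locate an effect in time. The group main effect averages in the pre-program visit: a constant 0.5 SD effect becomes (0 + 0.5 + 0.5 + 0.5)/4 = 0.375 SD over four visits.

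**The case against.** The best defense is that this is a condensed article. Contrasts, sphericity corrections and missing-data rules commonly sit in an analysis plan that is not shown, and their absence is no fault. The article never says that soldiers with a missing visit are excluded; that follows from the classical method. Imputation before the ANOVA would avoid it. All of this stands. What remains is that the article does choose the method, and as normally run that method sits badly with the missing data it expects.

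Several stronger readings are tempting but not supported:

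- A reader might infer that ANOVA cannot give effects at 4 or 12 months. It can, through planned contrasts; the article simply names none.
- A reader might count 46 instead of 58 per arm as a cost of ANOVA. It is 58 × 0.8, the plan's own dropout allowance, and no model observes 12-month values for soldiers who have left.
- A reader might apply the three-follow-up losses to every outcome. Biological and autonomic measures have two follow-ups. If the psychosocial ANOVA used only inclusion, 4 and 12 months, as that objective might suggest, the smaller losses apply there too.
- A reader might see a contradiction with "Scale variables will be treated as ordinal data and analyzed as above". That sentence follows text on descriptive presentation and mainly governs it. If it barred ANOVA, it would equally bar a linear mixed model.

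The concern that distressed or overloaded soldiers skip sessions is plausible but conjectural.

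**Conclusion.** The point holds as a weakness in the stated method for secondary outcomes. Under assumed independent misses of 5% to 10% per follow-up, classical repeated measures ANOVA discards 14% to 27% of soldiers for questionnaires and 10% to 19% for biological and autonomic measures. The precision loss is material with scattered misses and small at 12 months if missingness is almost all dropout. Bias is a possibility, not a demonstrated fact. The overall tests need visit-specific contrasts before they answer the objectives.

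A reader might infer that a mixed model would repair the secondary comparisons altogether. The documents do not support that. Individual randomization is ruled out in the Randomization section, and Participant Timeline mentions two companies. If each company forms one arm, program and company are confounded under either method. The primary chi-square comparison is not touched by this point.

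**What to change.** In Statistical Methods, replace repeated measures ANOVA with a linear mixed model for repeated measures:

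- All available visits, including inclusion, as outcomes; group, visit and group-by-visit as fixed effects; unstructured within-soldier covariance.
- Report the between-group difference in change from inclusion at 4 and 12 months for biomarkers and psychosocial factors, and at 6 and 12 months for the resilience scores.
- For the vulnerability objective, add vulnerability status and its interaction with group and visit, so that effect modification is still tested.
- Log-transform skewed biomarkers.

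Inclusion should be an outcome, not a covariate. A baseline-covariate model drops soldiers with no follow-up, and when allocation is not individual it can disagree with an analysis of change. A workshop-group random effect is not usable as a general term, because the nonintervention arm has no workshops.

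The cost is a change of analysis wording; standard software suffices and no new data are needed. There are two limits to state alongside it: the model relies on data being missing at random, and it cannot remove confounding with company.

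### The inputs to the vulnerability clusters differ between Objective 2.1 and Statistical Methods; read literally they include outcome markers, and the comparison as written has no arm term to absorb regression to the mean

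*Protocol article*

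**What the plan says.** Two sections of the protocol article, Objective 2.1 and Statistical Methods, describe the biological basis of vulnerability, and a third, Visit +12 Months, touches on it.

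- Objective 2.1: Vulnerability gives two biological components: "Innate: based on a study of the polymorphism of genes involved in stress regulation mechanisms" and "Acquired: based on miRNAs that target regulatory phenomena established in earlier work". Its third component is not biological: "General psychological and somatic symptomatology (the PHQ-15, HADS, and PCL-5".
- Visit +12 Months: End of Study, in listing what is not repeated after inclusion, describes the vulnerability sample as genetic polymorphism only.
- Statistical Methods states: "Vulnerability will be initially identified using a cluster analysis of the measured biological variables". The method is k-means or a "Gaussian model mixture, depending on the distribution", and the most at-risk cluster is labelled vulnerable. There is no list of inputs and no reference back to Objective 2.1.

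The next step is: "The effect of the intervention as a function of vulnerability status will be evaluated using repeated measures ANOVA, by comparing vulnerable and nonvulnerable groups". No outcome is named for this analysis, and no arm term.

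Objective 2.3 lists oxidative stress, central nervous system, inflammation, hypothalamic-pituitary-adrenal and autonomic measures under "We will assess the following regarding change in physiobiological biomarkers of activation and deterioration". They are biological, taken at inclusion, and analysed for change. Objectives of the Research sets the time of classification: "We will study levels of vulnerability at inclusion".

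**The concern.** The sections do not give the same set of cluster inputs, and the wider set overlaps with the outcomes. A soldier placed in the at-risk cluster partly because an inclusion value happened to be extreme will tend to have a less extreme value at +4 and +12 months, whatever the program does. A vulnerable-versus-nonvulnerable comparison of change on that same marker would then show vulnerable soldiers improving more. The secondary objective asks how vulnerability at inclusion bears on the program's effectiveness, so an artefact of this kind could be taken for the answer.

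**Working it through.** **Do the Objective 2.3 markers enter the clusters?** The Statistical Methods wording is unrestricted, and these markers are biological and measured at inclusion. K-means and Gaussian mixtures suit continuous variables, which genotypes are not. That favours the wide reading but does not settle it, since miRNA levels are also continuous. The wide reading is therefore literal, not explicit.

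**What follows if they do.** The plan gives no figure of its own to reproduce here. For a marker in SD units, let follow-up be Y1 = r·Y0 + noise, with no program effect and no time effect. Then E(Y1 − Y0 | Y0) = −(1 − r)·Y0. If the clusters differ by Δ on that marker at inclusion, the spurious difference in change is −(1 − r)·Δ.

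**Inputs.** From Sample Size: 58 per group with 20% loss, so 58 × 0.8 = 46.4, taken as 46 completers per arm and 92 in all. Assumed, because the article gives none: the number of markers, their intercorrelation and the retest correlation r.

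**First set of assumptions:** 10–15 markers, intercorrelation 0.1–0.3, two-cluster k-means on inclusion values, change in one clustered marker compared by t-test at 5%.

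- With 92 soldiers the simulated difference in change runs from −0.17 SD (at r = 0.7) to −0.49 SD (at r = 0.5). Dividing by 1 − r gives Δ = 0.17/0.3 = 0.57 and 0.49/0.5 = 0.98 SD.
- At r = 0.9 the same Δ would give 0.1 × 0.57 = 0.06 to 0.1 × 0.98 = 0.10 SD.
- False positives at r = 0.5–0.7: roughly 13–40% within the intervention arm and 20–65% with arms pooled. At r = 0.9: about 6–10% and 10–16%.
- The arm × vulnerability × time interaction on the same kind of data: 3–7%.

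**Second set of assumptions:** 3 or 10 markers, with a stable shared factor carrying 30% of true-score variance (observed intercorrelation 0.3 × r, so 0.15–0.27). Here the clusters partly capture lasting differences, so there is less regression to the mean. False-positive rates at a nominal 5%:

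| Markers | r | Intervention arm only | Arms pooled | Arm × vulnerability × time |
|---|---|---|---|---|
| 3 | 0.5 | 31.2% | 49.5% | 3.9% |
| 3 | 0.7 | 21.4% | 32.5% | 5.0% |
| 3 | 0.9 | 7.9% | 13.9% | 4.9% |
| 10 | 0.5 | 10.9% | 14.9% | 4.4% |
| 10 | 0.7 | 5.9% | 8.9% | 5.1% |
| 10 | 0.9 | 6.3% | 7.5% | 5.1% |

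The first row shows why the interaction holds. In the intervention arm the mean changes are −0.170 (vulnerable) and +0.168 (nonvulnerable), a difference of −0.338 SD. In the nonintervention arm they are −0.171 and +0.163, a difference of −0.334 SD. The artefact is the same in both arms, and the difference between arms is −0.338 + 0.334 = −0.004 SD.

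**With the outcome marker out of the clusters,** or with clusters built on independent variables, all three tests reject in 3.9–6.1% under the second set of assumptions.

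**The case against.** The strongest reply is that the biological variables in the clustering sentence are simply those that Objective 2.1 names, so the sections agree and only a list is missing, which an article may leave to the full protocol. That reading is possible. But the article itself describes the inputs in two places and does so differently, and its unrestricted wording, if followed, gives a wrong result on any marker that is both input and outcome.

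A second reply is that the program's effectiveness is judged on the composite of PANAS, Self-Compassion Scale and DRS-15. None of these is biological, so none can be a cluster input. This stands: the artefact does not directly reach them. It does not dispose of the point, because the same paragraph sends the secondary markers to repeated measures ANOVA and does not say which outcomes the vulnerability analysis covers.

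The third reply is the most important. An effect of the intervention as a function of vulnerability is properly an arm × vulnerability × time interaction, and regression to the mean cancels there. This also stands, with two limits. The stated comparison is vulnerable against nonvulnerable, with no arm term. And the Randomization section rules out individual randomization, so equal regression in both arms is not assured.

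A reader might infer that the plan certainly classifies soldiers on its own outcomes, or that its answer on who benefits is biased. The documents do not support either. Entry of the Objective 2.3 markers is a literal reading, and the bias depends on that reading, on the outcome chosen and on the missing arm term.

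**Conclusion.** The mismatch in cluster inputs is in the text. Its consequence is conditional: where a marker is both cluster input and analysed outcome, and the test is vulnerable-versus-nonvulnerable change, regression to the mean alone can produce a finding. Under the first set of assumptions the null rejection rate is roughly 13–40% within the intervention arm and 20–65% pooled at r = 0.5–0.7, falling to about 6–10% and 10–16% at r = 0.9. With 10 markers sharing a stable factor it is lower, at most 10.9% and 14.9%. All these rates rest on assumed correlations. The primary chi-square comparison is untouched and the composite's scales are not directly affected. The point concerns one secondary objective and should be corrected there because the correction is cheap.

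**What to change.** Make three changes.

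1. Use one list of cluster inputs, all measured at inclusion, in Objective 2.1, Visit +12 Months and Statistical Methods.
2. Add to Statistical Methods: *No variable analysed as an outcome in the vulnerability comparison is an input to the cluster analysis.*
3. Add: *The effect of the intervention by vulnerability is tested by the arm × vulnerability × time interaction; change in vulnerable versus nonvulnerable soldiers alone is not interpreted as an effect of the program.*

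The second and third changes complement each other. Exclusion protects fully only if the remaining inputs share no transient variation with the outcome. The interaction covers what is left when the arms are comparable.

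The cost is a few sentences and no new data. The clusters would rest on fewer inputs, and some genotypes may be missing because Ethical Considerations makes the genetic part optional. The handling of soldiers without a genotype should be stated with the list. If polymorphisms are kept as inputs, the clustering method should be one that accepts categorical variables.
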